#### Interventions

2.5.4

All patients will maintain the basic treatment: methimazole and levothyroxine sodium tablets (both from Merck & Co, LTD, Germany). Dosage will be adjusted every 28 days according to the patient's thyroid function level.

Experimental group: Pingmu Decoction combined with acupuncture treatment.(Acupuncture points: Shangtianzhu, Fengchi, Sanyinjiao, Hegu, Waiguan and Yangbai are the main points, together with Cuanzhu on the head and face, Yuyao acupoints, Sizhukong acupoints, Toulinqi acupoints, Qiuhou acupoints, Qingming acupoints, Fengchi acupoints and opticoels. The index finger will be taken dajian acupoints, xiaojian acupoints wood acupoints;the pinkies will be taken Yanhuang acupoints, Huoxi acupoints;the legs will be taken Yichong acupoints. Erchong acupoints and Sanchong acupoints. Calvaria will select Baihui acupoint. All acupoints will be pierced vertically except Cuanzhu. Yuyao and Sizhukong acupoints. Frequency of acupuncture treatment: 45 minutes of needle retention twice a week). Control group 1: (Pingmu Decoction group): Patients will be given Pingmu decoction orally, 2 times a day, 1 bag each time. Control group 2 (acupuncture group): The patients will be treated only with acupuncture(acupuncture and moxibustion locations are the same as those of the experimental group). The course of treatment will be 12 weeks.

#### Test the drugs and acupuncture illustrations

2.5.5

The drugs used in the clinical trials are Pingmu Decoction, made by The Longhua Hospital affiliated to Shanghai University of Traditional Chinese Medicine(Shanghai, China). Pingmu Decoction consists of Radix Astragali(Huangqi)15 g, Herba Epimedii(Yinyanghuo)12 g,

Miltiorrhiza(Danshen)15 g, Sinapis Alba(Baijiezi)9 g, Oldenlandia Diffusa(Baihuasheshecao)30 g, Semen Plantaginis(Cheqianzi)30 g, etc.

Decoction 200 ml/ bag, twice a day, 1 bag each time.

The acupuncture needles are provided by Suzhou Medical Supplies Factory Co, Ltd (Suzhou, China), specification: 0.25 × 25 mm. Production license number is Su Yao Food supervision apparatus production permit 20010020.

### Randomization and allocation

2.6

We will randomize all included patients using a table of random numbers. The 120 patients will be randomly divided into the experimental group, control group 1 and control group 2 in a 1:1:1ratio according to the treatment order.

### Outcomes

2.7

#### Primary outcomes

2.7.1

Exophthalmos degree. Measurement of prominence of the eyeball: Use the ocular protrusion measuring instrument (model YZ9) to measure the degree of exophthalmia(Which brand is called Crane and produced by Suzhou liuliu Vision Co., LTD.)TCM syndrome integral

According to the diagnostic criteria of Deficiency of Yang qi and blockage of phlegm and blood stasis formulated in 2002 edition of Clinical Research Guidelines for New Chinese Medicine.^[11]^ Main symptoms: fear of cold, lack of power, eyeball swelling pain; Secondary symptoms: tepid limbs, pale face, self - perspiration. The body of the tongue is fat or normal, the tongue is pale purple, or there are petechial spots, or the veins under the tongue are purple and angry. The tongue coating white greasy, pulse heavy fine astringent. According to the degree of occurrence of the main symptoms: no, mild, moderate and severe, they will be recorded as 0, 2, 4 and 6 points respectively, and according to the degree of occurrence of secondary symptoms: no, mild, moderate and severe, they will be recorded as 0, 1, 2 and 3 points respectively. The tongue image and pulse image of the block syndrome of phlegm and blood stasis will be scored 1 and 0 points according to whether they are consistent with deficiency of Yang qi and blockage of phlegm and blood stasis. TCM syndrome integrals will be recorded once before and after treatment in the three groups.

Efficacy of TCM symptoms will be determined by integral method: Efficacy index(n) = ((post-treatment score − pre-treatment score)/(pre-treatment score)) × 100%

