**Methods/Design::**

A prospective, randomized controlled clinical trial will be conducted to evaluate the efficacy and safety of Pingmu Decoction combined with acupuncture in the treatment of non-active thyroid-related eye disease in patients with Yang qi deficiency and phlegm-blood stasis syndrome. A total of 120 patients with non-active thyroid-related eye disease, namely deficiency of Yang qi and blockage of phlegm and blood stasis, are randomly divided into 3 groups and treated for 12 weeks. All three groups will maintain basic western medicine treatment. The primary outcomes are to observe the degree of prominence of eyes, and the TCM syndrome scores. The secondary result is clinical efficacy. Free triiodothyronine (FT3), free thyroxine (FT4), thyroid stimulating hormone (TSH), and thyroid stimulating hormone receptor antibody (TRAb)will be used as the observation indicators in this study. In addition, adverse reactions will be observed and recorded as safety indicators.

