### Statistical analysis

2.11

Statistical analysis includes statistical description and statistical inference. The statistical description of quantitative indicators includes mean, standard deviation, median, minimum and maximum. Qualitative indicators are described by frequency tables and component ratios.

All statistics will be analyzed by Statistical Packages of Social Sciences (SPSS) software (version 22.0). The continuous variables will be described using mean ± standard deviation. Continuous variables subject to normal distribution will be analyzed by Student *t* test. The Rank Sum test will be used for non-normal distribution data, ANOVA test will be used for comparison among three groups, wilcoxon test is used for non-normal distribution data. Enumeration datas will be expressed as rates, and the comparison of effective rates between groups are performed by X^2^ test. *P* < .05 will be considered statistically significant.

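### The co-primary TCM score is judged by percentage change from each patient's own baseline; the baseline-adjusted score in points would usually serve better, and one form should be fixed

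*Protocol article*

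**What the plan says.** The abstract (Methods/Design) states: "The primary outcomes are to observe the degree of prominence of eyes, and the TCM syndrome scores". Section 2.7.1 builds the score from three main symptoms ("no, mild, moderate and severe, they will be recorded as 0, 2, 4 and 6 points respectively"), three secondary symptoms ("no, mild, moderate and severe, they will be recorded as 0, 1, 2 and 3 points respectively") and a present/absent mark for tongue and pulse. On timing it says "TCM syndrome integrals will be recorded once before and after treatment in the three groups". The section then closes with "Efficacy of TCM symptoms will be determined by integral method: Efficacy index(n", the index being the post-treatment minus the pre-treatment score, divided by the pre-treatment score, as a percentage.

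Section 2.11 offers a t test or rank test for continuous variables, adds that "ANOVA test will be used for comparison among three groups", and says that "the comparison of effective rates between groups are performed by X^2^ test". It does not say whether the post-treatment score, the change or the index enters the three-group comparison. No use of the pre-treatment score as a covariate is mentioned.

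**The concern.** A score in points and a percentage of the patient's own baseline are different variables. They can rank the arms differently and give different P values from the same data. The article uses both for a co-primary outcome, and the one it says decides efficacy is the ratio.

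The ratio has two weaknesses. It makes a point of improvement worth more in a patient who starts low, so the arm comparison depends on the spread of baseline scores. It is also an inefficient way to use the baseline unless outcomes really scale in proportion to it. At stake are a lower chance of detecting a real benefit on the TCM outcome, and room for the choice of form to follow the result. Neither depends on the sign of the index, which is negative for improvement as written.

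**Working it through.** **Inputs from the protocol article**

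- Score range (2.7.1): 3 × 6 + 3 × 3 = 27, plus 1 or 2 for tongue and pulse, so a maximum of 28 or 29.
- Index (2.7.1): (post − pre)/pre × 100%.
- Size (2.4): 40 per arm less 10% loss, 40 × 0.9 = 36 evaluable per arm; α = 0.05. That calculation is for exophthalmos. The article gives no power figure for the TCM score, so there is none to reproduce.

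**Step 1: weighting (no assumptions)**

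One point of change is worth 100/pre percentage points on the index.

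- A 4-point fall from 6: 4/6 = 67%. From 24: 4/24 = 17%. The weights differ by 24/6 = 4 times.
- A 3-point fall from 5, 10 and 20: 60%, 30% and 15%.

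**Step 2: power of the index against the adjusted score (assumed inputs)**

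Simulation with three arms and 36 per arm. Assumptions: baseline mean 15, baseline SD 4 to 6, residual SD 3.5, slope of post-treatment on baseline score 0.5 to 0.9, and an effect of 2.5 points or the equivalent proportion of baseline. Across all 18 settings:

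| Variable tested | Power |
|---|---|
| Percentage index | 30-83% |
| Post-treatment score adjusted for baseline | 85-88% |

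The unadjusted post-treatment score and the index gave different verdicts in 20-49% of trials.

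**Step 3: how far this depends on the assumptions**

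A second set, also 36 per arm and three-group tests at 0.05, used baseline mean/SD of 14/3, 14/5 and 10/4 and varied the baseline-outcome correlation and the form of the effect. Power of the index minus power of each alternative, in percentage points:

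| Alternative | Lowest | Highest |
|---|---|---|
| Unadjusted post-treatment score | −15 (0.70 v 0.85; correlation 0.3, SD 5) | +48 (0.92 v 0.44; multiplicative effect, SD 5) |
| Plain change in points | −16 | +13 |
| ANCOVA on baseline | −19 | +6 |

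- The index exceeded ANCOVA only in the purely multiplicative scenarios, by 1 to 6 points. Elsewhere it was level or lower.
- With a true effect, verdicts from the post-treatment score and the index differed in 10-51% of trials. Verdicts from plain change and the index differed in 0-20%.
- With no effect, the post-treatment score and the index differed in about 6-8% of trials, and type I error stayed near 5% for each form taken singly.

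**The case against.** **A reader might infer a flat contradiction between the abstract and 2.7.1.** The text does not force that. An abstract may name the instrument while the methods section gives the measure derived from it. This objection stands: the fault is a primary variable that is not clearly fixed. On that milder reading, however, the ratio is what decides efficacy, so the case against the ratio applies in full.

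**A reader might infer that the index simply loses power.** It does not in general. The article's own alternative is an unadjusted score, and the index often beats it. Under purely multiplicative effects the index also edges past ANCOVA. The power argument holds against the baseline-adjusted score, usually but not always.

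**The choice of test variable and covariates is commonly left to an SAP, which is not shown.** This is fair as to silence, and the missing covariate in 2.11 is not held against the article as an omission. But 2.7.1 is not silent: it states that a ratio will decide TCM efficacy, and that choice can be improved.

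**The low-baseline example may not be eligible.** Section 2.5.1 requires the TCM syndrome by a cited standard, which may imply a minimum score. The article states none, and the source is not at hand. So it is not shown that patients with few symptoms would drive the comparison. The unequal weighting follows from the formula at any spread of baselines.

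**Disagreement between two tests of moderate power is expected and shows neither to be wrong.** True. It shows only that the choice of form matters and should be made before the data are seen.

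**Conclusion.** The point holds in limited form. Section 2.7.1 ties TCM efficacy to a percentage of the patient's own baseline, the abstract names the score itself, and 2.11 does not settle which is tested. The unequal weighting is arithmetic and needs no assumptions. The loss of power, about 30-83% against 85-88% for the baseline-adjusted score, and the 20-50% disagreement with the post-treatment score rest on assumed means, SDs, slopes and effects, because the documents give none for this score. Disagreement with plain change is smaller.

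The trial is not invalidated. A form that is usually more efficient is available from data already collected, which makes this a cheap improvement.

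**What to change.** In 2.7.1, name one TCM primary variable: the TCM syndrome score in points after 12 weeks of treatment. State there, and in 2.11, that arms are compared by ANCOVA with the pre-treatment score as covariate. Replace the sentence that makes the index decide efficacy with one saying that the percentage index is reported descriptively, without a P value.

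The cost is about one sentence in each section. Both scores are already recorded, so no new data are needed. The downside is that a percentage familiar to TCM readers becomes descriptive only. If effects were in truth purely proportional, a few points of power might also be given up (1 to 6 in the scenarios above).

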#### Secondary outcomes

2.7.2

Evaluation criteria of Western medicine curative effect:Obvious effects: symptoms such as eye distension, tearing, foreign body sensation, photophobia, burning pain, etc. basically disappeared; bulbous conjunctiva congestion and periorbital edema significantly subsided; symptoms of eye movement disorder and blepharoptosis basically returned to normal; protrusion degree decreased by ≥2 mm. Effective: the ocular symptoms and ocular signs are improved, and the protrusion degree is reduced by ≥1 mm, but the above indicators are not achieved. Useless: no significant improvement before and after treatment.

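### The TCM efficacy index has the opposite sign to its name, and the Western efficacy grades leave mixed responders without a clear grade

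*Protocol article*

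**What the plan says.** Two response measures are defined in section 2.7 of the protocol article.

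**TCM index (2.7.1, Primary outcomes).** Main symptoms are graded "no, mild, moderate and severe, they will be recorded as 0, 2, 4 and 6 points respectively" and secondary symptoms "no, mild, moderate and severe, they will be recorded as 0, 1, 2 and 3 points respectively", so a higher total is worse. The score is recorded before and after treatment in all three groups. The section then states "Efficacy of TCM symptoms will be determined by integral method", with an efficacy index built from "post-treatment score − pre-treatment score)/(pre-treatment score" as a percentage. It prints no cut-offs or categories for this index.

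**Western efficacy grades (2.7.2, Secondary outcomes).** There are three grades.

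- Obvious requires symptoms essentially gone and signs clearly subsided, ending with "symptoms of eye movement disorder and blepharoptosis basically returned to normal; protrusion degree decreased by ≥2 mm".
- Effective requires that "the ocular symptoms and ocular signs are improved, and the protrusion degree is reduced by ≥1 mm, but the above indicators are not achieved".
- The lowest grade reads "Useless: no significant improvement before and after treatment". It is not worded as everyone else.

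Section 2.11 compares effective rates between groups by a chi-square test. It names t, ANOVA and rank tests for continuous data and mentions no covariate.

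**The concern.** The index contradicts the scale printed beside it. A quantity called efficacy should rise when patients get better, and this one falls. It is attached to the TCM score, one of the two primary outcomes, so a results table, or a responder grading built on the index, could be read the wrong way round.

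The Western grades pose a different problem. Effective joins three conditions with *and*, while the lowest grade describes an absence of improvement. Between these two lie patients who improved on one or two components. The rate compared by chi-square is not defined until they are placed. The article does not say where they go, and it describes no sham, placebo or blinded grading that would protect a case-by-case decision.

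**Working it through.** **Index.** Inputs: the formula and the symptom scale in 2.7.1. The starting score of 20 is chosen for illustration.

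| Pre | Post | As written, (post − pre)/pre | Reversed, (pre − post)/pre |
|---|---|---|---|
| 20 | 0 | −100% | +100% |
| 20 | 6 | −70% | +70% |
| 20 | 14 | −30% | +30% |
| 20 | 20 | 0% | 0% |
| 20 | 26 | +30% | −30% |

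The magnitudes are right and the sign is opposite to the name. Multiplying every value by −1 leaves two-sided t, ANOVA and rank-test P values unchanged. A threshold is different. For any positive cut-off c, (post − pre)/pre ≥ c means post ≥ (1 + c) × pre, which only patients who worsen can meet. At an illustrative 30%, the patient going from 20 to 26 would count as a responder and the patient going from 20 to 6 would not.

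**Grades.** Take symptoms improved or not, signs improved or not, and a protrusion reduction either below 1 mm or from 1 to under 2 mm. Read the wording literally, with improvement on any component counting as improvement.

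| Symptoms | Signs | Below 1 mm | 1 to under 2 mm |
|---|---|---|---|
| Not improved | Not improved | Useless | no grade |
| Improved | Not improved | no grade | no grade |
| Not improved | Improved | no grade | no grade |
| Improved | Improved | no grade | Effective |

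Of 8 combinations, one is Effective, one is Useless and 6 have no grade.

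**Possible size of one part of the gap.** Section 2.4 gives a preliminary reduction with herbal medicine of 1.9 ± 1.1 mm. Assuming a normal distribution:

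- P(reduction < 1 mm) = Φ((1 − 1.9)/1.1) = Φ(−0.82) = 0.207. In an arm of 40 this is 40 × 0.207 = 8.3 patients.
- This is the share below 1 mm. The ungraded share is q × 0.207, where q is the fraction of these patients with some relief of symptoms or signs. The document does not give q.
- Assuming q from 25% to 75%, and this distribution in all arms: 120 × 0.207 × 0.25 = 6.2 and 120 × 0.207 × 0.75 = 18.6, so about 6 to 19 of 120.
- With an assumed mean of 1.0 to 1.9 mm and SD of 1.1 to 1.3 mm, P(< 1 mm) ranges from 21% to 50%. At 50% the same q range gives 120 × 0.50 × 0.25 = 15 to 120 × 0.50 × 0.75 = 45 of 120.
- Patients with at least 1 mm but unchanged symptoms or signs come on top. Nothing in the document allows them to be counted.

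**Effect on the rate.** Let E be Obvious plus Effective, U the clearly Useless, X the ungraded, and n = E + U + X. The rate is E/n if X count as failures, (E + X)/n if they count as successes, and E/(E + U) if they are left out. The first two differ by X/n. At 1.9 ± 1.1 mm, and for the below-1 mm part alone, that is 0.25 × 20.7% = 5.2 to 0.75 × 20.7% = 15.5 percentage points.

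**The case against.** On the index, the formula is ordinary percent change, and a negative value correctly means a lower score. The primary outcome is the TCM score itself, which the sign does not touch. That stands. A reader might infer that the index misclassifies patients or overturns the primary comparison. The article supports neither: it prints no thresholds, and two-sided tests give the same result under either sign.

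On the grades, the lowest step of a three-step scale can be read as the remainder. Section 2.4, though its wording is unclear, treats a reduction of at least 1 mm as what counts, which suggests that relief with less than 1 mm is a non-response. This is a fair reading and narrows that part of the gap. It does not close the other part. A patient with a 1.5 mm reduction and unchanged symptoms would have to be labelled as showing no significant improvement, against the same 1 mm threshold.

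It is also fair that many partial responders are graded. Symptoms and signs improved with at least 1 mm is Effective, and so is a reduction of 2 mm or more with incomplete resolution, provided symptoms and signs improved.

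Two further inferences are tempting. One is that 21% of patients are ungraded. That figure is only the share below 1 mm, and those among them with no relief are plainly Useless. The other is that ungraded patients will be dropped or graded with bias. The article does not say so, and it does not state whether assessors are blinded. What can be said is that the rule leaves the choice open.

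**Conclusion.** Both defects are in the printed text, and neither is a detail that an article would normally leave to an analysis plan.

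The index has the wrong sign for its name. This is a labelling error with no effect on two-sided P values. It would do harm only in interpretation, or if a positive threshold not shown here were applied to it.

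The grades are the weightier part. They are not exhaustive as worded, so the defect is non-classification, not placement in a wrong grade. The effective rate is not fixed until mixed responders are assigned. The number affected cannot be derived from the document. The range of 6 to 19 of 120 rests on normality, on the preliminary herbal-medicine figures holding in every arm, and on an assumed 25% to 75% with relief. It covers only one part of the gap. If the ungraded share were equal across arms and one rule were applied throughout, the difference in rates between E/n and (E + X)/n would be the same. The comparison is at risk when that share differs between arms or patients are placed case by case.

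**What to change.** **Index (2.7.1).** Write it as (pre-treatment score − post-treatment score)/pre-treatment score × 100%, or keep the formula and call it percent change, with a note that negative means improvement. Use it descriptively. Compare groups on the post-treatment TCM score adjusted for the baseline score. Both scores are already collected, so this needs no new data and improves on an unadjusted comparison.

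**Grades (2.7.2 and 2.11).** Before any data are seen, define the lowest grade as all patients who do not meet Obvious or Effective. State that the effective rate is (Obvious + Effective) divided by a fixed denominator, and name that denominator. Every combination in the table above then falls in exactly one grade.

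**Cost.** A few sentences in 2.7 and 2.11. The effective rate may come out slightly lower than if mixed responders were counted as successes or left out.

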#### Secondary outcomes

2.7.2

Evaluation criteria of Western medicine curative effect:Obvious effects: symptoms such as eye distension, tearing, foreign body sensation, photophobia, burning pain, etc. basically disappeared; bulbous conjunctiva congestion and periorbital edema significantly subsided; symptoms of eye movement disorder and blepharoptosis basically returned to normal; protrusion degree decreased by ≥2 mm. Effective: the ocular symptoms and ocular signs are improved, and the protrusion degree is reduced by ≥1 mm, but the above indicators are not achieved. Useless: no significant improvement before and after treatment.

### Safety assessments

2.8

Pingmu Decoction has been widely used in clinical practice, and has been found to be safe in clinical trials. Patients will be closely monitored for adverse reactions during this trial. In addition, laboratory tests will be performed at the beginning and end of the trial, including blood, urine, fecal, kidney, and liver function tests. If adverse events are reported, we will provide appropriate treatment to participants immediately.

### Participant timeline

2.9

The study will last 12 months, from November 10, 2020 to November 10, 2021. Recruitment will start in November 10, 2020. The recruitment process is shown in Figure 1.

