### Study design

2.1

This is a prospective, randomized controlled clinical trial with three parallel arms. We will recruit 120 patients from The Longhua Hospital affiliated to Shanghai University of Chinese Medicine. All patients will be randomly assigned to the experimental group (Pingmu Decoction + acupuncture), control group 1 (Chinese medicine group) and control group 2 (acupuncture group). All patients will maintain basic treatment for thyroid-related eye disease: methimazole and levothyroxine sodium tablets (both from Merck & Co, LTD, Germany). Dosage will be adjusted every 28 days according to the patient's thyroid function level. Control group 1 (Chinese medicine group), Pingmu Decoction will be required to take orally twice a day, 1 bag each time., control group 2 (acupuncture group) will be treated with acupuncture alone. The experimental group was treated with pingmu Decoction combined with acupuncture. All treatments will be administered for 12 weeks.

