### Study participants

2.3

We will recruit patients from the outpatient department of Longhua Hospital affiliated to Shanghai University of Chinese Medicine. The planned recruitment period is 12 months.

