### Sample size calculation

2.4

In this study, it is stipulated that only when the anterior ophthalmic process is reduced by ≥1 mm can be promoted. Exophthalmus references standard deviation is 1.3 mm, preliminary tests showed that Chinese herbal medicine could reduce the protrusion degree by 1.9 ± 1.1 mm,^[9,10]^ so we chose to reduce degree of exophthalmus to calculate the sample size, according to the α = 0.05, β = 0.1, σi is overall standard deviation for each group, μi means the population mean of each group is 1.3, K refers to the number of sample groups are 3, μ = Σμi/k, ψ of value through the check ψ of table that is 2.52, the formula for sample size = ψ2(Σσi2/k)/[Σ(μi−μ)2/(k−1)] calculated sample size is equal to about 36, considering a 10% loss to follow-up, determine the test each sample size for 40 cases, The total sample size is 120.

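### Twelve months of recruitment inside a 12-month study leaves no time for the 12-week course and post-treatment assessment of patients enrolled after 18 August 2021

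*Protocol article*

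**What the plan says.** Four statements in the protocol article bear on the schedule.

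- **Study length (section 2.9, Participant timeline):** "The study will last 12 months, from November 10, 2020 to November 10, 2021".
- **Start of recruitment (same section):** "Recruitment will start in November 10, 2020", which is the study's first day.
- **Length of recruitment (section 2.3, Study participants):** "The planned recruitment period is 12 months".
- **Length of treatment (section 2.1, Study design):** "All treatments will be administered for 12 weeks". Section 2.5.4, Interventions, agrees: "The course of treatment will be 12 weeks".

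On outcome timing, section 2.7.1 says of one of the two primary outcomes: "TCM syndrome integrals will be recorded once before and after treatment in the three groups". It gives no measurement day for the other, exophthalmos. Since the sample size rests on a reduction in exophthalmos, a value after the 12-week course is the natural reading.

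On numbers, section 2.4 concludes: "The total sample size is 120". It reaches this from about 36 per group: "considering a 10% loss to follow-up, determine the test each sample size for 40 cases".

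**The concern.** Recruitment and the whole study have the same start date and the same length, so they also share an end date. Nothing is left between the last enrolment and the study end, yet each patient needs 12 weeks to reach the post-treatment assessment. The stated durations cannot all hold if recruitment uses its full window.

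What is at stake is which of two things gives way. If the end date is enforced, patients enrolled late have a baseline but no post-treatment value for the primary outcomes, and that loss comes on top of ordinary dropout. If the end date is not enforced, the study finishes later than stated. The article does not say which applies, so the choice could be made during the trial rather than in advance.

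**Working it through.** **Inputs**
- Study: 10 November 2020 to 10 November 2021 (section 2.9).
- Recruitment: starts 10 November 2020 (section 2.9) and lasts 12 months (section 2.3).
- Treatment: 12 weeks = 84 days (sections 2.1 and 2.5.4).
- Sample: 120 patients, 40 per group, from 36 per group with 10% loss (section 2.4).
- Assumptions: treatment starts on the day of enrolment, and the post-treatment assessment falls on day 84. Any gap between enrolment and treatment, or between treatment and assessment, makes the fit tighter.

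**Step 1. The plan's own figures.** 10 November 2020 to 10 November 2021 is 365 days, or 12 months, as stated. 36 / (1 − 0.10) = 40 per group and 3 × 40 = 120, also as stated. Each figure is right on its own; the conflict is between them.

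**Step 2. Latest enrolment that fits the stated end.** 10 November 2021 − 84 days = 18 August 2021. The usable window is 365 − 84 = 281 days, or 281 / 30.4375 = 9.2 months.

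**Step 3. Earliest end that fits 12 months of recruitment.** 10 November 2021 + 84 days = 2 February 2022. The study would then last 365 + 84 = 449 days, or 449 / 30.4375 = 14.8 months.

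**Step 4. Patients affected if both statements are followed literally.** The article gives no accrual rate, so this step needs an assumption.
- Even accrual over 365 days: 84 / 365 = 23.0%, and 0.230 × 120 = 27.6, about 28 patients or 9 per group. That leaves 92.4 / 3 = 30.8, about 31 per group, before any ordinary loss.
- The allowance in section 2.4 is 10% of 120 = 12 patients.
- The 36 per group is a number after loss. The like-for-like figure is 30.8 × 0.9 = 27.7, about 28 per group.
- Accrual complete by 18 August 2021 (281 days): none affected.
- Even accrual that finishes early, after R days: 120 × (R − 281) / R patients are affected. This equals 12 when R = 281 / 0.9 = 312 days. Below that, the late recruits alone would not use up the allowance.
- Back-loaded accrual: more than 28.

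**Step 5. Accrual rate needed.** Over 12 months, 120 / 12 = 10 patients a month. Over 9.2 months, 120 / 9.23 = 13 a month.

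**The case against.** The strongest reply is that no outcome need be lost. The article does not say that follow-up stops, that data are cut off or that the database closes on 10 November 2021. It does say that all treatments run for 12 weeks, and a site would normally complete the course and assess a patient already enrolled. Section 2.9 may also use the word study loosely for the recruitment window, since it goes straight on to the start of recruitment and a figure of the recruitment process. That figure is not shown. Finally, 12 months is a planned period, and recruitment could reach 120 sooner.

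Much of this stands. A late finish is as plausible as missing outcomes, and the count of 28 depends on even accrual. What does not go away is the conflict in the written dates. If the study means only recruitment, the stated end is not the study's end. If recruitment finishes by mid-August, it does not take 12 months. Either way one section needs correcting. Nor is this detail that a condensed article may leave to a fuller document: the figures are stated, and they disagree.

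A reader might also infer a specific loss of power. The documents do not support one. Section 2.4 gives neither the three group means nor a between-group difference, so any power figure would rest on an effect chosen by the reader.

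**Conclusion.** The inconsistency is real and should be corrected. Section 2.3, section 2.9 and the 12-week course in sections 2.1 and 2.5.4 cannot all hold for a recruitment window that is fully used. The dates of 18 August 2021 and 2 February 2022 follow from the article's own figures, with assessment taken at the end of the course.

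The consequence is conditional. Enforcing the stated end would cost about 28 of 120 post-treatment outcomes under assumed even accrual, with a range from near 0 to more than 28 depending on the accrual pattern, against 12 allowed for loss. Not enforcing it means an overrun of up to about 12 weeks and no loss from this source. It would go too far to conclude that the trial will lose these outcomes or fall below 36 evaluable patients per group, because no cut-off on the end date is stated. The analysis method, the allocation and the type I error are not affected.

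**What to change.** Reconcile sections 2.3 and 2.9 in one of two ways.

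1. **Keep the study end of 10 November 2021.** State that enrolment closes by 18 August 2021, and change the recruitment period in section 2.3 to about 9 months. The cost is accrual of roughly 13 patients a month instead of 10.
2. **Keep 12 months of recruitment.** Move the study end in section 2.9 to at least 2 February 2022. The cost is about 12 more weeks of study time.

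In either case, add a sentence saying that every enrolled patient's post-treatment assessment is included in the analysis, so that the calendar end does not remove late recruits. Any matching dates in the trial registration should be brought into line. The change is one of dates only and leaves the 12-week course and the sample size as they are.
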